# The efficacy and safety of 'antianxiety granule' for anxiety disorder: a multicentre, randomized, double-blind, placebo-controlled, parallel-group trial

**DOI:** 10.1186/s13063-020-4057-1

**Published:** 2020-01-23

**Keywords:** Generalized anxiety disorder (GAD), Traditional Chinese medicine (TCM), RCT, Efficacy, Safety

## Abstract

**Background:**

Anxiety disorders are the most prevalent class of lifetime disorders in China, and generalized anxiety disorder (GAD) is one of the most common but frequently overlooked anxiety disorders. Conventional pharmacological treatments for GAD have varying degrees of side effects, dependency, and/or withdrawal syndromes. Traditional Chinese medicine (TCM) is considered a valuable therapeutic option for anxiety disorders and a potentially effective technique to reduce the side effects associated with antipsychotic drugs. This trial aimed to evaluate the clinical efficacy and safety of Antianxiety Granule, a granular Chinese medicine compound, for treatment of GAD.

**Methods/design:**

The current work is a multicentre, randomized, double-blind, placebo-controlled, parallel-group clinical trial with a 6-week treatment schedule. The study consists of three periods: a 1–7-day screening period, a 6-week primary treatment period, and a 1-week follow-up period. Follow-up assessments will be conducted 1 week after the last visit with a face-to-face interview or by telephone. The clinical efficacy of Antianxiety Granule for the treatment of GAD will be evaluated by examining the change in the Hamilton anxiety scale (HAMA) score, state-trait anxiety inventory (STAI) score, and TCM symptom scale in patients with GAD who receive daily TCM treatment. Moreover, an intention-to-treat (ITT) analysis will also be used in this randomized controlled trial (RCT).

**Discussion:**

Our study is a multicentre, randomized, double-blind, placebo-controlled, parallel-group trial to evaluate the safety and efficacy of Antianxiety Granule for the treatment of GAD. The results of this trial will provide valuable clinical evidence for the treatment of GAD.

**Trial registration:**

Chinese Clinical Trial Registry, ChiCTR1800016039. Registered on 8 May 2018.

## Background

Anxiety disorders are the most common lifetime mental disorders. A previous study [1] showed that approximately 3.6% of the global population suffers from an anxiety disorder, and the prevalence of anxiety disorders increased by 14.9% from 2005 to 2015. Because of the comparatively high prevalence, anxiety disorders are a major cause of disability and a substantial disease burden. Nevertheless, anxiety disorders are not taken seriously and are undertreated [2].

Generalized anxiety disorder (GAD) is not well-identified compared with other anxiety disorders [3]. A previous study reported that, even though the combined lifetime prevalence of GAD has been estimated at 3.7%, and it is commonly diagnosed in primary care settings, the lifetime prevalence in China is only 1.0% [4]. Individuals with GAD present with excessive, uncontrollable worry and persistent anxiety that typically lasts for at least 6 months. They continually express fears that they or their families will get sick or suffer an accident, and the feelings are associated with a variety of physical symptoms, such as fatigue, muscular tension, light-headedness, heart palpitations, dizziness, motor restlessness, disturbed sleep, etc. [5, 6]. All of these symptoms can seriously interfere with daily life and may cause functional impairment in patients with GAD. GAD is associated with high rates of comorbid disorders, increasing the risks of mental and physical health conditions [7]. Therefore, increasing social stress and a lack of effective anxiety management will result in greater healthcare resource utilization and an increased economic burden for individuals with GAD.

Currently, the treatment of GAD includes pharmacological and non-pharmacological treatments. Pharmacological treatments include selective serotonin-reuptake inhibitors (SSRIs) and serotonin-norepinephrine reuptake inhibitors (SNRIs), most antidepressants, several benzodiazepines, pregabalin, and buspirone [8]. Antipsychotic medication is the cornerstone treatment for psychotic disorders, but approximately 80% of mental health service users who are taking antipsychotic medication experience numerous, less severe, but nonetheless troubling side effects [9, 10]. Although these drugs exert certain clinical effects, they are associated with varying degrees of side effects, dependence, and withdrawal syndromes; side effects may often vary and be experienced at the same time, including sedation, hypersomnia, insomnia, sexual dysfunction, dry mouth, constipation, urinary problems and dizziness, chronic sedation, and a lack of concentration, all of which interfere with daily life activities [10–12]. Thus, long-term use of these treatments in GAD is discouraged. Patients with GAD may experience reduced benefits and increased harm following the chronic administration of these medications. Patients with anxiety disorders who are concerned about the side effects of pharmacological drugs may preferentially select non-pharmacological treatments, such as applied relaxation, psychotherapy, cognitive therapy, mindfulness interventions, etc. [13–16]. However, it is theoretically difficult to master psychotherapeutic techniques, and mastery of these techniques takes a long time. In China, traditional Chinese herbal medicine (TCHM) has a long history in the treatment of anxiety disorders with certain characteristics. Herbs such as chamomile [17] and *Scutellaria lateriflora* [18] have anxiolytic activities. TCHMs are usually used in combination. Currently, there have been few clinical trials on the efficacy of herbal compounds in individuals with GAD. Because of the treatment effects and few side effects, TCHMs are widely accepted by patients; however, to date there are still not enough standardized, strict, modern, clinical controlled trials on TCM.

In the current study, a multicentre, randomized, double-blind, placebo-controlled, parallel-group clinical trial was designed to evaluate the clinical efficacy and safety of the Chinese medicinal compound Antianxiety Granule for the treatment of GAD.

## Methods/design

### Setting and design

This study is a multicentre, randomized, double-blinded, placebo-controlled, parallel-group, 6-week treatment, clinical trial. Eligible participants will be randomly assigned to an intervention group (Antianxiety Granule) or placebo group at a ratio of 2:1. The participants will be recruited from the following six hospitals: Shanghai Municipal Hospital of Traditional Chinese Medicine, Shanghai Seventh People’s Hospital, Shanghai Chinese and Western Medicine Hospital, The Fifth People’s Hospital of Shanghai, Fudan University, Jingan District Hospital of Traditional Chinese Medicine, and Yangpu District Hospital of Traditional Chinese Medicine. The study consists of three periods: a 1–7-day screening period, a 6-week primary treatment period, and a 1-week follow-up period. Participants will be assessed at baseline and at the 2nd, 4^th^, and 6th week after the initiation of the intervention. Follow-up assessments will be conducted 1 week after the last visit by face-to-face interviews or by telephone (Fig. 1). In this study, the clinical efficacy of Antianxiety Granule will be assessed for the treatment of GAD by examining changes in the Hamilton anxiety scale (HAMA) score, state-trait anxiety inventory (STAI) score and the TCM symptom scale in patients with GAD who receive daily TCM treatment. The flowchart of the study process is presented in Fig. 1, and the timing of the treatment visits and data collection is presented in Table 1.

**Fig. 1 Fig1:**
[figure not shown]
Flowchart of the study trial. HAMA, Hamilton anxiety scale; STAI, State-trait anxiety inventory; TCM, traditional Chinese medicine; ITT, intention to treat

**Table 1 Tab1:**
[figure not shown]
Schedule of enrolment, interventions, and assessments

^a^Laboratory tests: blood, urine, feces, electrocardiogram, kidney and liver function. *HAMA* Hamilton Anxiety Scale, *STAI* State-trait anxiety inventory, *TCM Symptom Scale* traditional Chinese medicine symptom scale

### Participants

#### Inclusion criteria

The study inclusion criteria are as follows:
The participant is a male or female outpatient aged 18–70 yearsThe participant meets the diagnosis criteria for GAD (International Classification of Diseases, 10th Revision (ICD–10) and Diagnostic and Statistical Manual of Mental Disorders Fifth Edition (DSM-5th)) and has met the symptom criteria for at least 6 monthsThe participant has never taken anxiolytic agents or has stopped anxiolytic agents for at least half a monthThe participant has a HAMA score > 14The participant is highly adherent, will take the granule for 6 weeks, and will participate in follow up 1 week laterThe participant is diagnosed with a TCM syndrome-type according to the *Diagnosis and Treatment Scheme for Anxiety Disorder of TCM*, consistent with the TCM Internal Medicine and the Mental Illness key specialties of the Shanghai Municipal Hospital of Traditional Chinese MedicineThe participant participates voluntarily; signed informed consent is requiredSeverity: the participant has experienced poor psychosocial functioning and has feelings of unbearable pain and the inability to escape

#### Exclusion criteria

The exclusion criteria are as follows:
The participant has an organic psychosyndrome or an anxiety disorder caused by psychoactive substances, another medical condition (e.g., hyperthyroidism), or non-addictive substancesThe participant is currently pregnant or lactating or is of reproductive age and is not willing or unable to cease contraceptive use during treatmentThe participant has obvious heart, liver, kidney, or other systemic symptomsThe participant’s laboratory tests and electrocardiogram (ECG) show clinically significant abnormalities, and the investigators shoud judge the results can influence the evaluation of the granule or the participant’s safetyThe participant’s aspartate aminotransferase (AST) or alanine aminotransferase (ALT) levels exceed two times the upper limit of normalThe participant has participated in other drug clinical trials within the previous 4 weeksThe participant has a Hamilton depression scale (HAMD) score ≥ 18

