### Interventions

Eligible participants will receive an Antianxiety Granule or placebo treatment twice daily for 6 weeks according to their random assignment. The Antianxiety Granule is composed of *Cyperi rhizoma*, *Amomum aurantiacum*, *Cinnamomi cortex*, *Curcumae radix*, *Radix salviae*, *Gardeniae fructus*, *licorice*, *Polygala tenuifolia*, *Albizia bark*, *Polygoni multiflori caulis*, and *Daylily.* The herbs will be mixed into brown, bitter, herbal extract granules, and the placebo will consist of one-tenth of the Antianxiety Granule. Both the Antianxiety Granule and placebo will have an identical appearance, colour, and smell. All granules will be packaged in sealed, opaque single-dose sachets with similar labelling. Participants will receive two packaged dose bags (14 doses per bag) every 2 weeks, three times in total, and they will be requested to return the unused granules to the research teams. The use and returning of the granules will be noted on the case report forms (CRFs) by the researchers. All participants will receive some transportation allowances at the end of the trial.

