### Safety assessment and adverse events

Safety will be monitored throughout the trial. Routine laboratory safety tests (including routine tests of blood, urine, liver function (ALT, AST), and kidney function (blood urea nitrogen (BUN) and creatinine (Cr)) will be performed at the screening visit and visit 5. Safety will also be assessed through monitoring adverse events (AEs) and vital signs throughout the 6 weeks of treatment. AEs are defined as unexpected symptoms, signs, or diseases that occur during treatment, and all participants will be instructed to report any abnormal event. If AEs happen, the investigators will evaluate the relationship between the AE and the intervention. All AEs will be reported in detail on the CRF. The schedule of enrolment, interventions, assessments, and data collection is presented in Table 1.

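### The contraception exclusion is worded the wrong way round: as printed, women of reproductive age are eligible only if they stop contraception during treatment

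*Protocol article*

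**What the plan says.** The relevant item in the protocol article's Exclusion criteria has two parts. The first excludes a participant who is pregnant or breastfeeding at entry. The second, in the same sentence, excludes a participant who "is of reproductive age and is not willing or unable to cease contraceptive use" for the duration of treatment.

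Other sections fix the setting in which this rule operates:

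- Inclusion criteria: men and women aged 18 to 70 are eligible, so the trial admits women who could become pregnant.
- Interventions: "Eligible participants will receive an Antianxiety Granule or placebo treatment twice daily for 6 weeks". The product has 11 listed herbal components, and "the placebo will consist of one-tenth of the Antianxiety Granule", so both arms receive some of the active material.
- Safety assessment and adverse events: routine laboratory tests "will be performed at the screening visit and visit 5". The text names blood, urine, liver and kidney tests.
- Recruitment: candidates are assessed against the inclusion and exclusion criteria before they sign consent.
- Trial status: protocol version 2 was approved on 2 May 2018, the first participant was randomized in August 2018, and recruitment was continuing when the article was written.

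**The concern.** A trial that excludes pregnant women normally goes on to require that women who could conceive avoid pregnancy while on study drug. Here the second part of the criterion asks for the opposite. A woman who uses contraception and means to continue is screened out, while one who gives it up is let in. The first part keeps pregnancy out on the day of entry, and the second removes protection against it for the following 6 weeks.

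What is at stake is participant safety and a correct statement of who is eligible. Any pregnancy on treatment would be exposed to the herbal compound, at full strength in the granule arm and at one-tenth in the placebo arm, in a trial whose stated purpose includes safety.

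**Working it through.** The article gives no figure on this point to reproduce, and the question needs no arithmetic. The check is to read the rule literally, work out whom it admits, and look for anything elsewhere in the article that changes the answer.

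**Step 1: the rule and its complement.** As printed, exclude if pregnant, or lactating, or (of reproductive age and (unwilling or unable to stop contraception)). The complement is: admit if not pregnant, not lactating, and (not of reproductive age, or both willing and able to stop contraception).

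**Step 2: apply it to cases.** Each woman below is neither pregnant nor lactating at entry. The last column uses the apparent intent, which is to exclude those unwilling or unable to use contraception.

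| Participant | Rule as printed | Apparent intent |
|---|---|---|
| Reproductive age, uses contraception, will continue | Excluded | Admitted |
| Reproductive age, uses contraception, will stop for the trial | Admitted | Excluded |
| Reproductive age, uses none and plans none | Admitted (nothing to stop) | Excluded |
| Not of reproductive age | Admitted | Admitted |

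The two versions disagree in all three rows for women of reproductive age and agree only where the rule does not apply. Changing the one verb from stopping to using contraception reverses those three rows and makes both parts of the item serve the same aim.

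**Step 3: look for a correction or a reason elsewhere.** The Inclusion criteria, Recruitment, Interventions, and Safety assessment and adverse events sections contain no requirement to use contraception. They describe no interaction with hormonal contraceptives that could justify stopping them, and no substitute method or abstinence rule. So nothing in the article overrides or explains the sentence. The absence of a named pregnancy test is not part of this point: the Table 1 grid is not shown, and such detail may lie in the full protocol.

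**Step 4: whom it covers.** The sentence speaks of participants, not women. Reading it as a rule for women follows from the pregnancy and lactation wording beside it.

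**The case against.** The strongest reply is that this is a one-word slip in an English-language article and that no site need have acted on it. The dates lend this some weight. The article appeared on 23 January 2020, about 17 months after the first randomization in August 2018, so it cannot have been the published source for the earlier screening. The Recruitment section says that candidates are assessed against the criteria, but not that staff use this text. Whether version 2, the consent form or the CRF carries the same word cannot be seen. This stands, and it limits what can be claimed about conduct. It does not make the sentence right: either the operative documents share the error, or the article misstates who was eligible.

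A second reply is that the item refers to contraceptive drugs only and leaves other methods open. That is conceivable, but the wording is unqualified and the article gives no reason for such a ban.

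A reader might also infer more than the document supports:

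- **A strict contradiction.** There is none in logic. One can exclude women pregnant at entry and also ask others to stop contraception. The conflict is one of purpose.
- **A number of pregnancies.** The article gives neither the share of women of reproductive age nor a conception rate. Assume shares of 20% to 40% and 6-week risks of 2% to 20%: the result runs from 252 × 0.20 × 0.02 = 1.0 to 252 × 0.40 × 0.20 = 20.2. That twentyfold spread comes entirely from the assumptions. It also applies one risk to every such woman and subtracts nothing for pregnancies that would occur under any rule. It should carry no weight.
- **Lost primary outcome data.** The article states no withdrawal rule for pregnancy, a withdrawn participant could still be rated, and the Statistical analyses section handles missing primary values by last observation carried forward.
- **Eligibility that differs by centre.** This is possible if some sites follow the text and others assume the reverse, but nothing in the article shows that it has happened.

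**Conclusion.** The criterion is wrong as written and should be corrected promptly. Followed literally, it admits women of reproductive age only if they stop contraception, and so defeats the pregnancy and lactation exclusion in the same sentence. A drafting or translation error is the likeliest explanation.

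The conclusion rests on the plain wording of the sentence, on the reading that it concerns women, and on the absence of any correcting text in the article. It does not assume that any site has applied the wording or that any pregnancy has occurred. Its importance comes from the direction of a safety safeguard, not from a count. No effect on sample size, power, alpha or the Hamilton anxiety scale analysis is claimed.

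**What to change.** 1. Replace the second part of the item with a rule that excludes a participant of reproductive age who is unwilling or unable to use effective contraception during treatment. The clinical team should settle which methods count as effective.
2. Check approved protocol version 2, the consent form and the CRF eligibility page for the printed wording.
3. If any of them carries it, amend it, notify all sites at once, and ask each site which rule it has applied. If none does, publish a correction to the article.
4. Review any pregnancies on study now, pooled and blinded. The Randomization, allocation, and blinding section keeps the codes closed during the trial, so report pregnancies by arm only after unblinding.

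The cost is a one-sentence amendment or correction, a check of existing forms and, if needed, a notice to sites. It needs no extra participants, visits or procedures.

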### Sample size

A sample size of 252 participants will be recruited on the basis of the pre-post trial. On the basis of previous results and considering an anticipated participant dropout rate of 20%, with a significance level of 0.05, 252 patients will be needed. These 252 patients will be randomly divided into two groups (168 participants in the Antianxiety Granule group and 84 participants in the placebo group, in a ratio of 2:1).

### Recruitment

The participants will be recruited via advertisement posters on bulletin boards in the hospital. If they are willing to participate, they can initially be screened by phone to determine if the basic criteria are met. Then, participants will be further assessed face to face by professional researchers. Once the participants are evaluated with the inclusion or exclusion criteria and volunteer to participate, the researchers will explain the study procedure in detail, and they will be asked to sign a written informed consent form before the intervention begins.

All participants can withdraw their consent at any time during the trial.

### Randomization, allocation, and blinding

The random allocation schedule will be generated by [name]., Professor of Medical Statistics, Head, Department of Biostatistics, Shanghai Jiao Tong University School of Medicine (SJTU_SM). Participants will be randomized by computerized, permuted blocks using SAS version 9.4, and stratified by trial centre. The random allocation schedule (including the random numbers and block size) will be sealed in an opaque envelope to conceal group allocation, and allocation concealment will be maintained by the main study administrator/sponsor to avoid selection bias. The randomized allocation schedule and duplicated blinding codes will not be opened during the trial. Simultaneously, a corresponding emergency letter will be prepared for each participant, and the envelope containing the treatment mode will be marked with the participant number. The emergency letter will not be removed unless it is required to do so.

The study is a double-dummy treatment trial. Participants who meet the inclusion criteria will be randomly assigned to an intervention group (Antianxiety Granule) or placebo group in a ratio of 2:1. Neither participants nor attending study personnel will be able to identify the intervention group or placebo group by appearance, packaging, labelling, or shape of the treatment. All the researchers will receive training on the specifications of this study and will be asked to strictly adhere to those specifications.

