### Outcomes

#### Primary outcome

The primary outcome measure will be a change in the HAMA score [19]. The HAMA scale is the most widely used assessment tool for anxiety disorders in psychiatric clinical and scientific research. The HAMA scale is a 14-item observer-rating questionnaire that can be categorized into two orthogonal groups, “psychic” and “somatic” anxiety. The outcome will be assessed by the difference in the HAMA score from the baseline.

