### Quality control

The study will be conducted at five hospitals to guarantee its rigour and quality. The investigators will be trained to ensure the quality of the trial. All of the trial data will be fully integrated into the CRFs and monitored by the Clinical Research Centre of Drugs of the Shanghai Municipal Hospital of Traditional Chinese Medicine. Moreover, if any inconsistent data are identified, the primary data will be individually checked by the research monitor and the inconsistency will be reported. The database will be locked after it is reviewed and confirmed by the administrator and the inspector. The source data will be saved appropriately and patient-reported treatment guesses will be obtained to determine the success of blinding. Fisher’s exact test will be used to analyse the data.

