### Statistical analyses

The main analysis will follow the intention-to-treat (ITT) principle and will be done as follows: the full analysis set (FAS) will include the randomized participants who received any treatment and completed at least one follow up. The per-protocol set (PPS) will include patients who complied with the protocol. Only when the minimum compliance rate of participants who received the investigational drug is 80% will we use the PPS. Participants who have at least one randomized treatment will be included in the ITT and safety set (SS). To estimate missing primary outcome variables, data from the last study will be used as the final result following the last observation carried forward (LOCF) principle. Data will be analysed using the statistical software SAS version 9.4 or SPSS 20.0.

Sociodemographic variables will be analysed by the *t* test for continuous variables. Matched data will be compared using the Wilcoxon test, and categorical variables will be analysed using the chi-squared test. Change across time of the primary and secondary outcomes will be analysed by repeated measures analysis of variance (ANOVA). We will use ANOVA for randomized block design if the variance and covariance matrix meet the sphericity assumption. ANOVA for repeated measurement data may have two types of error: errors among subjects are the errors corresponding to treatment, and errors within subjects are the errors corresponding to time and the interaction between treatment and time. Significance is will be accepted when the two-sided alpha level is 0.05.

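### The described primary model names neither centre (the randomisation stratum) nor baseline HAMA as a covariate; adding both before unblinding is a nearly free gain in precision

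*Protocol article*

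**What the plan says.** All references are to the protocol article.

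- **Randomisation, allocation, and blinding:** "Participants will be randomized by computerized, permuted blocks using SAS version 9.4, and stratified by trial centre". Centre is the only stratification factor named.
- **Setting and design:** "Participants will be assessed at baseline and at the 2nd, 4^th^, and 6th week after the initiation of the intervention". Entry also requires a HAMA score above 14 (Inclusion criteria), so baseline HAMA is known for everyone.
- **Primary outcome:** "The outcome will be assessed by the difference in the HAMA score from the baseline".
- **Statistical analyses:** primary and secondary outcomes are analysed by repeated measures ANOVA. Its structure is given by its error terms: "errors among subjects are the errors corresponding to treatment, and errors within subjects are the errors corresponding to time", the within-subject part also covering the treatment-by-time interaction. No centre term and no baseline covariate is named. The section also mentions an ANOVA for a randomised block design, to be used if sphericity holds.
- **Number of centres:** Setting and design says "The participants will be recruited from the following six hospitals" and names them. Quality control says "The study will be conducted at five hospitals to guarantee its rigour and quality".

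**The concern.** A factor used to stratify randomisation is normally carried into the analysis. Stratified blocks balance the arms within each centre, so differences between centres do not add to the true variance of the treatment contrast. A model without centre still counts those differences as error, so its standard error is somewhat too large.

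Baseline is a separate matter. Subtracting it fixes its coefficient at 1. When the correlation between baseline and follow-up is below 1 and the SDs are similar, that over-corrects and adds noise that a fitted coefficient would remove.

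What is at stake is power. The Limitations section concedes that the sample is small, and 2:1 allocation leaves only 84 participants on placebo, about 14 per centre over six centres.

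**Working it through.** **Inputs from the article.** N = 252, split 168:84; 20% dropout; two-sided alpha 0.05; randomisation stratified by centre.

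**Inputs not in the article, therefore assumed.** Baseline to follow-up correlation rho, 0.3 to 0.7; share of change-score variance lying between centres (ICC), 0 to 0.10; an effect of 0.42 SD (0.419 before rounding); equal SDs at baseline and follow-up unless stated. The formulas treat a single follow-up comparison, as a simplification of the repeated measures analysis.

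**The plan's own figure.** The article gives no power, effect or SD, so 252 cannot be reproduced. Only the dropout step can be checked: 67/0.8 = 83.75, rounded up to 84, and 134/0.8 = 167.5, rounded up to 168. (70 × 1.2 = 84 and 140 × 1.2 = 168 fit as well.) I use 134:67 evaluable. The effect detectable with 80% power is then (1.96 + 0.842) × sqrt(1/134 + 1/67) = 2.802 × 0.1496 = 0.419 SD.

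**Step 1: baseline, variance.** With common SD sigma, the per-subject variance is 2(1 − rho)sigma² for the change score and (1 − rho²)sigma² with baseline as a covariate. The ratio is (1 + rho)/2.

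| rho | variance ratio | saving | sample size equivalent to 252 |
|---|---|---|---|
| 0.3 | 0.65 | 35% | 252/0.65 = 388 |
| 0.5 | 0.75 | 25% | 252/0.75 = 336 |
| 0.7 | 0.85 | 15% | 252/0.85 = 296 |

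**Step 2: baseline, power.** Power = Phi(0.419/(0.1496 × s) − 1.96), where s = sqrt(2(1 − rho)) for change and sqrt(1 − rho²) with the covariate.

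| rho | s, change | power | s, covariate | power |
|---|---|---|---|---|
| 0.3 | 1.183 | 66% | 0.954 | 84% |
| 0.5 | 1.000 | 80% | 0.866 | 90% |
| 0.7 | 0.775 | 95% | 0.714 | 97.5% |

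The 80% at rho 0.5 holds by construction, because the effect was chosen to give it.

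**Step 3: unequal SDs.** The HAMA entry threshold may narrow the baseline SD. Suppose it is 0.75 of the follow-up SD. The change variance becomes 1 + 0.5625 − 1.5 × rho (in units of follow-up variance), and the ratios are:
- rho 0.3: 0.91/1.1125 = 0.818, saving 18%
- rho 0.5: 0.75/0.8125 = 0.923, saving 8%
- rho 0.7: 0.51/0.5125 = 0.995, saving under 1%

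**Step 4: centre.** With centre-stratified blocks, the unadjusted standard error is too large by 1/sqrt(1 − ICC). True alpha = 2 × (1 − Phi(1.96/sqrt(1 − ICC))). Where the centre-adjusted test has 80% power, the unadjusted test has Phi(2.802 − 1.96/sqrt(1 − ICC)).

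| ICC of change | SE too large by | true alpha | power |
|---|---|---|---|
| 0 | 0% | 0.050 | 80.0% |
| 0.01 | 0.5% | 0.049 | 79.7% |
| 0.05 | 2.6% | 0.044 | 78.5% |
| 0.10 | 5.4% | 0.039 | 76.9% |

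**Step 5: simulation check.** Six centres of 42, blocks of 6 at 2:1, N = 252, rho 0.5, change-score effect 0.376 within-centre SD; 4,000 null and 2,000 alternative runs. At ICC 0, power was 80% on unadjusted change and 90% with baseline added. At ICC 0.10, it was 79% unadjusted, 81% with centre, 89% with baseline and 91% with both. Null rejection at ICC 0.10 was 0.0445 unadjusted and 0.052 centre-adjusted (Monte Carlo standard error about 0.003). The direction agrees with step 4, and the simulated conservatism is milder than the formula's 0.039.

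**The case against.** The strongest reply is that this is a condensed article. Covariate lists and stratum terms are usually left to the analysis plan, which is not shown, and the sentence on error terms could be read as a general description of the method rather than a closed list. Part of this stands: the full plan may already contain both terms. But the article is not merely silent. It sets out the model's structure, and that structure does not match the stated randomisation. Nor does the randomised block phrase supply centre. It depends on sphericity, a condition on repeated measurements within a subject, so the block is most naturally the subject.

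Three stronger readings are tempting, and the documents do not support them.

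- A reader might infer that baseline is ignored. It is not, since the outcome is a difference from baseline.
- A reader might infer that the standard error is wrong on both counts. Leaving out a baseline covariate that was not used in randomisation costs power but leaves the standard error valid. Only the omission of centre misstates it.
- A reader might infer a risk of false positives. The centre error goes the other way: the test is conservative, and exact if centres do not differ.

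It is also fair to say that the relevant ICC is that of the change score. Stable centre differences, such as rater leniency, cancel on subtraction, so a figure for raw HAMA cannot be used here.

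**Conclusion.** The point holds as a free improvement; the validity of the trial is not threatened. The described analysis gives up precision by using baseline only through subtraction, and becomes slightly conservative by omitting the stratification factor. Baseline is the larger part: a variance saving of 15% to 35% over rho 0.7 to 0.3 with equal SDs, and from under 1% to 18% if the baseline SD is three quarters of the follow-up SD. At high rho the power gain is small (95% to 97.5%). The centre part is minor and may be nil. These sizes rest on assumed values of rho, ICC, effect and SD ratio. The direction does not: apart from a few degrees of freedom, the covariate-adjusted analysis does no worse than raw change.

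The conflict between six and five hospitals is real but minor. The Discussion refers to the other five hospitals, which fits a lead site plus five, so the Quality control sentence looks like the outlier. It bears on this point only because it sets the number of centre levels.

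**What to change.** Before unblinding:

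1. Add baseline HAMA to the primary model as a continuous covariate, with a baseline-by-visit term, and state that baseline is then not also a response time point.
2. Add centre as a fixed effect.
3. Put the corresponding baseline score and centre in the STAI models.
4. Reconcile the hospital count between Setting and design and Quality control, so that the centre term matches the randomisation list.

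If the full analysis plan already has these terms, correcting the article's description is enough. The cost is wording and a few degrees of freedom: five for six centres and one for baseline, plus the baseline-by-visit terms, out of roughly 200 evaluable participants. Both variables are already collected. The article reports recruitment as ongoing, so at that date the change could still be made blind.
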